## Abstract

**Background:**

People at greatest risk for poor HIV outcomes include young (13-34) people of color who have sex with men. Individuals in this population are least likely to be aware of their HIV status and are at the highest risk for disengaging from medical care and antiretroviral therapy. The Positive Peers mobile app (PPA) was designed to engage this population with real-time social support, HIV and healthy lifestyle information, and medical management tools. We expect that greater PPA engagement will predict key HIV care outcomes. Study predictions are grounded in a user-centric model of digital media use and the perceived affordances of the PPA.

**Objective:**

This study aims to determine the optimal deployment of the PPA in clinical settings (at enrollment vs delayed start) and to compare intervention outcomes with a no-intervention, observation-only condition. The PPA is designed specifically for key HIV disparity populations, including younger sexual, gender, racial, and ethnic minorities.

**Methods:**

The Positive Peers Intervention Trial (PoPIT) is a multisite, randomized clinical trial designed to evaluate the effectiveness of the PPA as a tool for use in clinical settings. Trial arms compare the immediate deployment of the PPA with usual care and observation only. This protocol outlines a mixed methods design consisting of concurrent prospective self-report questionnaires, in-depth interviews with PPA users, and medical record review. PoPIT questionnaires include measures of social determinants of health, HIV-related stigma, perceptions of digital media use, self-efficacy, substance use, and social support. Multiple aspects of PPA intervention engagement are measured natively within the app. Outcomes include HIV National Quality Forum indicators and perceived HIV-related stigma.

**Results:**

The research protocol (1R01MD019185-01) was funded for US $903,363.00 in direct costs by the National Institute for Minority Health and Health Disparities on September 24, 2023, for 5 years. The study began recruiting patients on June 3, 2024, and will continue accrual until November 27, 2026.

**Conclusions:**

Findings will provide evidence of the usefulness of the PPA as a support tool in HIV clinical care. Primary results will inform optimization of PPA deployment and evaluate a theoretical model of user engagement with a mobile health management app. Qualitative data will provide a phenomenological description of intervention engagement and perceived user efficacy.

**Trial Registration:**

ClinicalTrials.gov NCT06388109; https://clinicaltrials.gov/ct2/show/NCT06388109

**International Registered Report Identifier (IRRID):**

DERR1-10.2196/87601

## Introduction

### Background

Younger people under the age of 35 continue to carry a disproportionate burden of HIV risk [1-4]. Within this group, social risk factors such as poverty, drug use, job insecurity, food scarcity, and housing instability present significant barriers to HIV testing, retention in care, and viral suppression [5,6]. These factors contribute to younger people being less likely to be retained in HIV care and to achieve sustained viral suppression, especially those in marginalized communities [1,7]. There is a critical need to establish effective and sustainable tools to address these barriers and improve HIV outcomes for disproportionately impacted young people [4,7].

Several electronic tools have been designed to engage young people with HIV (YPWH) in clinical care and to support medication adherence [8-10]. However, fewer tools link newly diagnosed and out-of-care clinical populations to a live peer cohort that shares the unique challenge of living with HIV [11]. Mobile health (mHealth) apps are gaining credibility as reliable and accessible communication modalities that provide a direct platform for addressing social barriers to adherence, retention, and viral suppression [10,12,13]. Implementation of mHealth interventions is particularly well suited to high-priority jurisdictions where PWH may be socially and geographically isolated from trustworthy information and reliable support [14-16]. The Positive Peers mobile app (PPA) was created in response to these needs as a clinical mHealth tool to help newly diagnosed young people, or those returning to care, connect with each other and learn about living with HIV [17].

### The Positive Peers Mobile App

PPA is a free, multifunction mobile app that features interactive functions organized around a Mind/Body/Spirit theme. The Mind theme is characterized by information provision, including more than 400 vetted articles concerning issues faced by YPWH, as well as first-person stories from current app users living with HIV. The Body theme offers tangible support in the form of interactive medication and laboratory reminders and trackers, and curated state-by-state community resources addressing a variety of living needs (clothing, housing, food). The Spirit theme fosters human connection through a community forum that allows users to ask questions and share experiences and encouragement, as well as a chat function for 1-on-1 conversations. The app is freely available to eligible young people (ages 13-34) who provide evidence of their HIV-positive status. App activity is monitored and supported by a group of trained app administrators at our home medical institution in Cleveland, Ohio, as well as at key partner locations across the United States.

Following development and successful feasibility testing with a pilot group [17], a cohort comparison medical record review of PPA users and clinically eligible but study-naïve nonusers showed that PPA users were significantly more likely to be regularly engaged in HIV care and to achieve higher rates of viral suppression than nonusers, particularly among young adults aged 13-24 [18]. This success, paired with positive reactions identified in qualitative work [19], provided the basis for planning a randomized controlled trial to evaluate the PPA as a clinical tool for supporting YPWH who are newly diagnosed or seeking care in 6 federally designated Ending the Epidemic priority jurisdictions in the United States [14].

The primary objective of the Positive Peers Intervention Trial (PoPIT) is to evaluate the impact of the mHealth app on engagement in care and viral suppression outcomes among newly diagnosed and reengaged young patients. Study research questions and hypotheses are informed by, and evaluated based on, social networking, media uses and effects, and social support theories.

### Social Networking Theory and Social Support

Social Networking Theory (SNT) is an approach to understanding how ideas and behaviors disseminate through relational ties [20]. A key line of research in SNT examines whether and how social networks influence health behavior [21,22]. SNT has guided thinking about information flow and innovation uptake for decades, with more contemporary approaches positioning social network membership as central to identity, community, and health [23-25]. Notably, although several mechanisms of influence have been postulated (eg, modeling, presentation of group norms), the source of behavior change in SNT approaches stems from social ties rather than individual cognition [26-28]. A key mechanism underlying social network effects is social support.

Although social support was initially conceptualized as a dyadic process (see [29]), health-related research has produced ample evidence of the efficacy and benefits of networked social support on various social media platforms, including reduced depression and mitigation of stigma [30-32]. As social media enables a more flexible, collaborative communication process, it offers greater opportunities for engagement with similar others [33-35]. Participants in online support groups have reported strong feelings of empowerment associated with exchanging information, receiving emotional support, experiencing validation and understanding, helping others, and sharing amusement [36,37]. These empowerment processes, in turn, are associated with feeling more informed, experiencing greater social well-being, demonstrating greater efficacy in interactions with physicians and in managing treatment, and greater acceptance of illness [38].

Among PWH, stronger social support has been associated with safer sex [39], better medication adherence [40], fewer disclosure-related concerns [41], lower depression [42], and better overall quality of life [31,43]. Not surprisingly, younger people, and those recently diagnosed with HIV, are more likely to use online rather than face-to-face support, a trend that reverses as they gain experience and begin to trust others [44,45]. Support messaging in this context most frequently takes the form of informational and emotional support [43,45].

Social networking among PWH particularly benefits younger, isolated, or marginalized people who report less in-person support [46]. Stress rooted in chronic illness is known to be associated with a greater prevalence of adverse mental and behavioral health outcomes [47,48]. Ongoing stressors, such as living with HIV, homelessness, or identifying with a population minority, can also motivate social media use and online support seeking [49]. Positive outcomes associated with stress-induced social media use include active coping, the creation of positive group norms, increased self-efficacy, and reduced perceived stigma [37,50-52]. Importantly, unique sources of stress can be mitigated through connection with similarly stigmatized others, particularly within a context of social support and expressed self-compassion [53-56]. The resulting sense of belonging, or social connectedness, generated in these situations can catalyze resilience, increased esteem, and potentially improved self-care [55,57]. These effects are known to be robust even within weak-tie social networks, such as those involving acquaintances [58]. The PPA leverages these processes and effects by providing a secure space where social connections with similar others can aid the management of ongoing chronic illness stressors. The PPA builds on these ideas by using HIV status as a criterion for belonging rather than exclusion, providing secure opportunities for individual or group communication, and disseminating information targeted to network characteristics.

### Digital Media Uses, Effects, and Affordances

The PPA app is informed by 2 user-centric theories of media use: media uses and effects theory and media affordances theory [59-63]. The media uses and effects approach is a model of media use that posits that needs experienced by users are expressed as motives, that is, intentions for media use [64]. Active user motives (eg, information- or support-seeking), rather than passive motives (eg, passing time), are associated with more direct information and affective processing, which further determine the likelihood of cognitive, affective, or behavioral change [65]. This paradigm has been useful for understanding internet use in general and social media effects in particular [61,66]. For example, Phua et al [24] established that social networking site design and interface features were associated with different motives for use and subsequent gratifications received from those sites.

Media affordances theory developed from the media uses and effects approach by accommodating the rapid evolution of technology as a mediator of human communication. Within media affordances theory, specific features, functions, or constraints of social media technology provide opportunities to act relative to a user’s needs or purposes within a given context [67,68]. Media affordances are defined as variable user perceptions of technology features that offer pathways for the gratification of perceived needs [69]. For example, interacting with a peer in the PPA community forum may address a user’s need for social inclusion in a more acceptable way than through a public social media platform, creating a perceived affordance associated with the app. Not all users perceive the same affordances of the same technology. Instead, users’ perceptions of app or device affordances emerge through interaction with that technology. For example, one person may use an mHealth app because it affords a confidential space to connect with similar others, whereas another may be drawn to a comprehensive medication tracking system. These theoretical frameworks suggest that user needs and perceptions of app affordances create a context for seeking gratification from that app that may or may not be reinforced. Experimentation and adaptation shape users’ perceptions of how an app can work for them. These related user-centric approaches to understanding media influence depict a communication process that accommodates variation in user-technology interactions [67,68]. Variability can be found in (1) user characteristics and needs, (2) technology design features, and (3) user-technology interactions and outcomes [68].

### Study Rationale and Objectives

We expect the PPA to support engagement in HIV care by normalizing and rewarding care visits, promoting health literacy, reducing stigma, and enhancing inclusion, thereby allowing users to help others with similar challenges. Our goal is to increase HIV viral suppression rates by at least 15% by offering practical and peer support through a smartphone app. Specific aims addressed by the protocol described in this manuscript are (1) comparing the effectiveness of HIV care supported by the PPA with usual care for improving retention in HIV care and viral suppression among high-priority adolescents and young adults with HIV; (2) identifying factors that predict user engagement with primary PPA components and associated effects on retention in care, viral suppression, and HIV-related perceived stigma; and (3) evaluating PoPIT implementation across sites and over time. Figure 1 illustrates the conceptual model of the PoPIT study’s influence and outcomes. This paper describes the protocol used to achieve these aims in a randomized clinical trial with a concurrent qualitative evaluation focused on user experience.

**Figure 1 figure1:**
[figure not shown]
Positive Peers Intervention Trial (PoPIT) study conceptual model. PPA: Positive Peers mobile app.

## Methods

### Study Design

Specific aims and corresponding hypotheses will be evaluated in a randomized controlled trial that compares HIV outcomes in patient groups randomized to either immediate or delayed access to the PPA. The delayed-start design is intended to ensure that both randomized study conditions receive identical study procedures, follow-up, reminders, incentives, and assessments during the first 6 months of participation. The only difference is the timing of app access. Any improvement observed in the delayed-start group during this period can therefore be attributed primarily to nonspecific effects of trial participation. The primary randomized comparison at 6 months thus estimates the incremental benefit of the app beyond these common trial effects. A greater improvement in outcomes in the immediate-start group at this point would provide evidence of a specific impact of the app.

Prospective questionnaires will be administered at baseline and at 3, 6, 9, and 12 months to provide evidence for model-specific hypotheses and the mediating effects of covariates and demographics. We have included an opportunity for patients who decline full study participation to grant permission to the PoPIT team to abstract their HIV outcomes from medical records on the same schedule as full study participants. This observation-only arm includes only the baseline questionnaire and medical record review of study outcomes. The inclusion of an observational cohort in the randomized controlled trial design strengthens external validity by enabling comparison of trial participants with the broader clinic population. By comparing outcomes from both randomized controlled trial arms with those of the observational cohort, we will gain additional insight into how trial participation may influence outcomes and how the intervention might be further adapted for a more diverse clinical population.

Allocation (1:1) to study conditions is determined by the REDCap system’s randomization module following signed consent and completion of the baseline questionnaire, and before PPA download. Participants are informed of their randomization assignment after completing the baseline questionnaire. If randomized to the immediate intervention condition, site staff assist the participant in downloading the PPA to their personal smartphone and orient them to the app’s functions and study guidelines. Participants randomized to the delayed-start arm receive usual clinic care before returning to the clinic 6 months later to download and begin using the app. This delayed-start cohort serves as a control group, allowing comparison of the effects of intervention exposure with usual care.

The Practical Robust Implementation and Sustainability Model (PRISM) was used to inform intervention implementation throughout the study [70,71] (Table 1). The PRISM model was selected because it accommodates multilevel and dynamic interactions among the intervention, stakeholders’ perspectives, and recipient characteristics. The PRISM model is an expansion of the well-used RE-AIM (ie, Reach, Effectiveness, Adoption, Implementation, and Maintenance) approach, with additional emphasis on sustainability factors both within and external to the study setting [70].

**Table 1 table1:** PRISM^a^-informed implementation plan for the PoPIT^b^ study.

RE-AIM^c^ domain	Before implementation	During implementation	After implementation
Intervention delivery	Estimate population parameters with site staff and set accrual benchmarks. Develop recruitment strategies with site staff.	Log and monitor recruitment and enrollment. Deploy boosting efforts if needed.	Calculate reach and enrollment trajectories.
Effectiveness	Preintervention site visits to determine setting and population characteristics, and resources.	Collect prospective questionnaire data. Medical record review. Conduct user qualitative interviews.	Primary and secondary outcome analysis and qualitative analysis of user interview data.
Adoption	Tailor recruitment materials for sites. Provide clear user support materials and training curriculum for site staff. Create instructional animations for PPA^d^ functions.	Track all admin requests for app assistance, addressing potential barriers as needed. Analyze native app engagement tracking. Review monthly performance trajectories.	Report adoption facilitators and barriers, construct app engagement variables, and track use and attrition trajectories over the project life.
Implementation	Deliver group and individual site trainings to promote fidelity. Design a REDcap^e^ data management system for onboarding and data collection.	Log site administrator app activity and user compliance with data collection. Conduct monthly all-site check-in meetings.	Postimplementation staff interviews.
Maintenance	Develop oversight strategies, meeting agendas, staff interview approach, and questions.	Monthly site staff meetings. Qualitative staff interviews.	Evaluate cost, review systems, identify potential adaptations, and determine dissemination prospects.

^a^PRISM: Practical Robust Implementation and Sustainability Model.

^b^PoPIT: Positive Peers Intervention Trial.

^c^RE-AIM: Reach, Effectiveness, Adoption, Implementation, and Maintenance.

^d^PPA: Positive Peers mobile app.

^e^REDcap: Research Electronic Data Capture.

Implementation planning with PRISM identified a set of evaluation activities before, during, and after the study that provide evidence of intervention exposure, effectiveness, staff adoption of study procedures, and intervention sustainability. A detailed description of the implementation plan and associated outcomes will be reported in a future manuscript.

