### Recruitment

Eligible persons seeking care or registered with a participating clinic are invited to participate in the study through their preferred contact channel on record with the clinic. They are asked by trained clinic staff at participating sites whether they would be interested in helping to evaluate a new HIV support app in a research study. Persons who agree to participate review the informed consent document with the study staff before any study procedures. Participants can earn up to US $250 in gift cards by completing study questionnaires and interviews. Participants receive US $50 for completing the baseline questionnaire and a qualitative interview, and US $25 for completing each follow-up questionnaire. There is also a monthly raffle for ecological momentary assessment (EMA) completion, in which participants have a chance to win an additional US $25 for completing an EMA questionnaire during that month. If a person declines participation in the randomized trial, they are asked whether they would participate in the more passive observational monitoring arm, which includes a baseline questionnaire and prospective medical record data collection. Participants in the observational cohort are compensated with a US $50 gift card at the time of study consent and completion of the baseline questionnaire.

A reliance review institutional review board (IRB) system is in place, with agreements from all sites to accept the lead study site IRB for regulatory oversight. The general consent form is written in simple, plain language and is devoid of logos and colors. One study site is required to use its own institution’s regulatory language; however, study information is consistent across all sites. The primary investigative team is clearly identified in the consent form, along with corresponding contact information.

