### Enrollment, Randomization, and Data Collection Procedures

All participants are consented, enrolled, and randomized at the partner institution where they receive care, in partnership with the PoPIT staff, who are needed to set up the user’s PPA account. Specifically, following in-person consent at the partner site, all participants complete a preloaded baseline questionnaire on a study-dedicated tablet in the presence of study staff. While they are completing the questionnaire, the trial participant is randomly assigned in REDCap to either the intervention (immediate PPA start) or control (6-month delayed PPA start) arm at a 1:1 ratio. Participants randomized to the delayed-start arm receive usual clinic care before beginning the clinical intervention. Given our pilot findings indicating a stronger PPA effect on HIV viral suppression among participants in the youngest age group (ie, <24 years), we employ a block randomization strategy in which study arm assignment occurs separately for participants within the age groups 13-24 and 25-34 years.

Following randomization, site study staff assist participants randomized to the immediate-start arm in downloading the PPA from the public app store using the participant’s personal phone. Site study staff guide participants through in-app tutorials demonstrating how to use app features. Participants randomized to the delayed-start arm are provided with a folder containing general HIV self-management information and contact numbers for the clinic and the site coordinator. Data are collected via online forms (enrollment and medical record review), questionnaires, and SMS text messaging. Participants are consented and enrolled by study staff in person, and the baseline questionnaire is completed independently at the same visit. Remaining follow-up questionnaires at 3, 6, 9, and 12 months are prompted by an SMS text message or email and completed online. Participants and study staff are aware of study arm assignment. Delayed-start participants are given app access after completing the 6-month questionnaire. Site study staff follow the same procedure to assist with downloading the app and reviewing tutorials for participants in both the immediate- and delayed-start arms.

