User engagement with interactive media comprises 4 validated attributes: (1) physical interaction, (2) interface assessment, (3) absorption, and (4) digital outreach [76]. Analyses indicate that greater physical interaction with the app and more positive assessments of the interface predict cognitive absorption with the content, which in turn is associated with stronger behavioral intentions to manage and socially share the content [76]. Our conceptual model has focused primarily on frequencies of physical interaction. EMAs can provide insight into user perceptions of the app interface and the extent to which users feel absorbed or attentive during use. We may also include a single-item measure of digital outreach in the form of the likelihood of recommending the app to others. Ultimately, we anticipate that increased user engagement will be associated with higher medication adherence, lower viral load, greater engagement in care, and reduced stigma. In this study, EMAs are delivered as SMS text messages sent to participants. The first EMA is deployed to all users 1 month after they begin using the app and focuses on physical interaction with the PPA (see Table 2). The second EMA is sent 2 months after app initiation and includes brief questions assessing current participant engagement with the PPA interface, as well as 4 items adapted from the System Usability Scale [77]. These micro-questionnaires serve as evaluative tools for assessing intervention implementation and effectiveness.

**Table 2 table2:** EMA^a^ items at time 1 and time 2.

EMA items			Response option

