**Time 1 EMA items: interaction with the PPA^b^**			
	Is the Positive Peers mobile app downloaded to your smartphone right now?	Yes/no	
	Did you use the Positive Peers mobile app today?	Yes/no	
	How many days in the last week did you use the Positive Peers mobile app?	Daily 4-6 days 2 or 3 days Once None	
	Did you take your medication yesterday?	Yes/no	

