### Quantitative Data Collection and Measures

Data collection is planned for a total of 18 months for each participant. Three modes of data collection are used in the study. First, site staff collect medical record data, including date of diagnosis, HIV viral load, T-cell counts, and office visit dates, for the 12 months before enrollment and for 18 months after enrollment.

Second, participants receive an email or SMS text message notification to complete follow-up electronic questionnaires at 3, 6, 9, and 12 months after enrollment. Automated reminders are sent on the scheduled completion date; if the questionnaire is not completed, additional reminders are sent 1 week and 2 weeks later. If the questionnaire coincides with an office visit or cannot be completed remotely for any other reason, study staff can administer the pending questionnaire on site using a laptop or iPad (Apple Inc). Delayed-start participants are onboarded to the app, either in person or remotely by site staff, 6 months after enrollment. This group completes baseline, 3-month, and 6-month questionnaires before downloading and initiating app use.

Third, during the intervention period, EMAs are used to collect in-the-moment information about app use (eg, “Is the Positive Peers mobile app currently downloaded to your phone?”) and related perceptions. PPA provides a natural technological interface through which such perceptions or behaviors, and their correlates within the app or the broader social environment, can be assessed in a nuanced, dynamic, and longitudinal framework.

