### Qualitative Data Collection

#### Longitudinal Semistructured Interviews and Interpretive Thematic Analysis

In-depth semistructured interviews with participants explore experiences with PPA initiation and use, including participants’ reflections on joining a mobile app community focused on HIV care. Interviews are conducted longitudinally at approximately 3, 7, and 11 months after initiating use within both immediate- and delayed-start cohorts, with largely independent samples of 8-10 participants from each cohort at each time point. Interviews explore how participants learn, navigate, and maintain PPA use, focusing on perceived benefits, costs, and motivations for ongoing engagement. Anchoring the convergence of mixed methods, interviews also elicit reflections on YPWH’s experiences with the study’s measured quantitative constructs (eg, experienced social needs that thwart or facilitate engagement in HIV care, perspectives and attitudes toward social media use, perceived self-efficacy for health management).

For sampling and analysis, participants are selected purposively to balance participation across key demographic strata of interest (eg, racial and ethnic identity, gender identity). All interviews are professionally transcribed verbatim and analyzed using NVivo (Lumivero) software with an interpretive, phenomenologically informed approach [94] and a constant comparative approach [95] to thematic analysis. Our approach to analysis is phenomenologically informed in that study participants share a core set of experiences related to their identities as YPWH. To enhance rigor and validity, a subgroup of 5 YPWH participants will serve as thematic auditors and critically respond to qualitative findings and interpretations.

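### The arms are said to differ only in app timing for 6 months, but the article's own schedule gives them different assessments, incentives and contacts

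*Protocol article*

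**What the plan says.** Study Design states that the delayed-start design is meant to ensure that "both randomized study conditions receive identical study procedures, follow-up, reminders, incentives, and assessments during the first 6 months of participation". The next sentence says, without qualification, that nothing but the date of app access separates the arms. The section then concludes that the 6-month comparison isolates what the app adds to effects common to all trial participants.

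Other sections time study activities from app start rather than from randomisation:

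- Ecological Momentary Assessments: "The first EMA is deployed to all users 1 month after they begin using the app"; a second follows 2 months after app start. In Table 2 the first EMA includes "Did you take your medication yesterday".
- Recruitment: "There is also a monthly raffle for ecological momentary assessment (EMA) completion", with a chance of US $25. A qualitative interview is also paid.
- Longitudinal Semistructured Interviews: "Interviews are conducted longitudinally at approximately 3, 7, and 11 months after initiating use", with 8-10 participants per cohort at each time point.
- Table 3: the affordances measure is given 3 and 6 months after app start.

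On month 6 in the delayed arm, Study Design says participants "receive usual clinic care before returning to the clinic 6 months later to download and begin using the app". Enrollment, Randomization, and Data Collection Procedures says "Delayed-start participants are given app access after completing the 6-month questionnaire". Quantitative Data Collection and Measures says "Delayed-start participants are onboarded to the app, either in person or remotely by site staff, 6 months after enrollment".

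**The concern.** The article justifies attributing the 6-month difference to the app by asserting that everything else is equal. If study contact, incentives and assessments also differ, the contrast estimates a package and not the app alone.

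The differences touch the outcomes in two ways. A text asking about medication bears on the behaviour behind viral suppression, and before month 6 only the immediate arm receives it. An onboarding contact at month 6 occurs only in the delayed arm, at the boundary of a window in which attendance and testing define the outcome. Clinical Outcomes requires an office visit with an HIV clinician per 6-month interval. Planned Statistical Analysis uses laboratory results per 6-month period and the 6-month viral load. Power Analysis treats a patient with no documented visit as out of care and unsuppressed.

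**Working it through.** **Step 1. Put app-timed events on the randomisation clock.** Study month = months after app start + 0 (immediate) or + 6 (delayed).

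| Activity | Immediate | Delayed |
|---|---|---|
| EMA 1, with the medication item | 1 | 1 + 6 = about 7 |
| EMA 2 | 2 | 2 + 6 = about 8 |
| EMA raffle opens | 1 | about 7 |
| First interview, subset | about 3 | 3 + 6 = about 9 |
| Affordances measure | 3 and 6 | 9 and 12 |
| App onboarding | 0 | 6 |

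Up to month 6 the immediate arm has two EMAs, raffle entry, a possible paid interview and up to two affordances assessments. The delayed arm has none of these. The scheduled 3- and 6-month questionnaires and their US $25 payments appear common to both arms.

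**Step 2. How much contact is this?** EMA 1 has one yes/no medication item; EMA 2 has none. With 250 randomised 1:1, an arm has 125 people, so 8-10 interviewees are 8/125 = 6.4% to 10/125 = 8%. The affordances measure falls at months when both arms have a questionnaire, so it may lengthen a contact rather than add one.

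**Step 3. Compare the month-6 descriptions.** One section has delayed participants coming back to the clinic; another allows remote onboarding; a third places access after the 6-month questionnaire. None calls onboarding an HIV-clinician visit or mentions a blood draw.

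**Step 4. The plan's power figure.** Inputs from Power Analysis: 0.60 versus 0.80, 106 per arm, two-sided 0.05, pooled Z test.

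Power = Φ{[Δ√n − 1.96√(2p̄(1−p̄))] / √(p₁(1−p₁) + p₂(1−p₂))}, where p̄ is the mean of the two rates.

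With Δ = 0.20 and p̄ = 0.70: (2.059 − 1.270)/0.632 = 1.247, so power is 0.894. This agrees with the stated 90%; the same formula asks for 109 per arm, within 3% of 106.

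**Step 5. Illustration for the onboarding contact only.** Assume that a share m of controls would otherwise have no visit or viral load by month 6, that a share f of these are tested because of onboarding, and that 60% of those tested are suppressed. The control rate becomes 0.60 + m × f × 0.60. None of these three inputs is in the article.

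| m | f | Control rate | Difference from 0.80 | Power, 106 per arm |
|---|---|---|---|---|
| any | 0 | 0.600 | 0.200 | 0.894 |
| 0.10 | 0.10 | 0.606 | 0.194 | 0.876 |
| 0.10 | 0.50 | 0.630 | 0.170 | 0.787 |
| 0.15 | 0.50 | 0.645 | 0.155 | 0.715 |
| 0.20 | 0.50 | 0.660 | 0.140 | 0.633 |

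The result depends almost wholly on f, and f is zero if onboarding is remote or prompts no test. No comparable calculation is possible for the EMA side, because the article gives no effect of such contact on suppression.

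**The case against.** **EMAs belong to the app.** Reminders and Notifications lists them as a type of PPA notification, most items concern the app, and the app has its own medication reminders, so one further text may add little. That limits the likely size. It does not rescue the claim: Quantitative Data Collection and Measures names EMAs as one of three data-collection modes, they go out by SMS, and the raffle is listed with the study payments. Assessments and incentives still differ.

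**The wording only states an intention.** The first sentence does; the sentence after it does not.

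**The delayed arm gets the same later.** True, but the claim covers the first 6 months.

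**Outcome windows belong in the analysis plan, which is not shown.** Fair, and a missing window rule is not the point. The point is a stated property that the schedule contradicts.

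Two stronger readings are tempting. A reader might infer that the month-6 contact does raise retention and viral-load ascertainment in controls, at a known cost in power. The documents do not support this: onboarding may be remote, and it is not described as a clinician visit or as including a test. A reader might also infer that the raffle or the interviews inflate the app's apparent effect on suppression. The raffle rewards answering an EMA, not attending or adhering, and the interviews reach few people.

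**Conclusion.** The assertion that only app timing differs is wrong on the article's own schedule, and the interpretation of the 6-month contrast rests on it. This part needs no assumption.

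The consequence for the estimate is unknown. EMA-linked contact, if it acts at all, would favour the immediate arm. An in-person onboarding contact, if it prompts visits or tests inside the window, would favour the delayed arm. Neither the net direction nor the size can be computed from the documents. The power figures, from 0.894 (no effect) down to 0.633, are illustrations for the second mechanism under assumed inputs and are not estimates of harm. Severity is moderate: the point changes what the 6-month result may be said to show, but does not undermine the randomised comparison.

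**What to change.** 1. **Common cut-off.** Close the month-6 outcome window on the same day after randomisation in both arms, set before delayed-arm onboarding, so that visits and viral loads on or after onboarding do not count toward the month-6 outcome. Cost: a date rule, and the loss of some results close to month 6 in both arms.

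2. **Reconcile the onboarding descriptions.** Study Design and Quantitative Data Collection and Measures should agree on how delayed participants are onboarded. Cost: wording.

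3. **Restate the contrast, or match the contact.** Replace the sole-difference sentence and describe the 6-month contrast as the effect of the app plus its linked EMA, raffle, interview and affordances contact. This costs only wording and covers everyone enrolled. Alternatively, for participants still to be enrolled (accrual runs to November 27, 2026), send the non-app EMA item with raffle entry to the delayed arm at months 1 and 2. That costs a REDCap messaging change and more raffle entries, and early and late enrollees would then have different procedures. The interviews and the affordances measure would still differ, so the sentence would need correcting anyway.

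Two remedies should be avoided. Excluding people interviewed before month 6 removes a purposively chosen group from one arm after randomisation. A rule about tests prompted by onboarding is unworkable, because the reason for a test is not among the listed record-review data.
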